## Abstract

**Background:**

Paroxysmal atrial fibrillation (AF) is a probable cause of cryptogenic stroke (CS), and its detection and treatment are important for the secondary prevention of stroke. Insertable cardiac monitors (ICMs) are clinically effective in screening for AF and are superior to conventional short-term cardiac monitoring. Japanese guidelines for determining clinical indications for ICMs in CS are stricter than those in Western countries. Differences between Japanese and Western guidelines may impact the detection rate and prediction of AF via ICMs in patients with CS. Available data on Japanese patients are limited to small retrospective studies. Furthermore, additional information about AF detection, including the number of episodes, cumulative episode duration, anticoagulation initiation (type and dose of regimen and time of initiation), rate of catheter ablation, role of atrial cardiomyopathy, and stroke recurrence (time of recurrence and cause of the recurrent event), was not provided in the vast majority of previously published studies.

**Objective:**

In this study, we aim to identify the proportion and timing of AF detection and risk stratification criteria in patients with CS in real-world settings in Japan.

**Methods:**

This is a multicenter, prospective, observational study that aims to use ICMs to evaluate the proportion, timing, and characteristics of AF detection in patients diagnosed with CS. We will investigate the first detection of AF within the initial 6, 12, and 24 months of follow-up after ICM implantation. Patient characteristics, laboratory data, atrial cardiomyopathy markers, serial magnetic resonance imaging findings at baseline, 6, 12, and 24 months after ICM implantation, electrocardiogram readings, transesophageal echocardiography findings, cognitive status, stroke recurrence, and functional outcomes will be compared between patients with AF and patients without AF. Furthermore, we will obtain additional information regarding the number of AF episodes, duration of cumulative AF episodes, and time of anticoagulation initiation.

**Results:**

Study recruitment began in February 2020, and thus far, 213 patients have provided written informed consent and are currently in the follow-up phase. The last recruited participant (May 2021) will have completed the 24-month follow-up in May 2023. The main results are expected to be submitted for publication in 2023.

**Conclusions:**

The findings of this study will help identify AF markers and generate a risk scoring system with a novel and superior screening algorithm for occult AF detection while identifying candidates for ICM implantation and aiding the development of diagnostic criteria for CS in Japan.

**Trial Registration:**

UMIN Clinical Trial Registry UMIN000039809; https://tinyurl.com/3jaewe6a

**International Registered Report Identifier (IRRID):**

DERR1-10.2196/39307

## Introduction

Stroke is a leading cause of mortality and disability worldwide. A primary goal of stroke management is to clarify the stroke etiology to optimize secondary prevention. Despite standard extensive diagnostic workups, approximately 15%-40% of all ischemic stroke cases are of unknown etiologies and are classified as cryptogenic [1]. Cryptogenic stroke (CS) is heterogeneous in origin, but most cases involve embolic mechanisms. Paroxysmal atrial ﬁbrillation (AF) is suspected to be a major cause of CS, and patients are likely to develop severe cerebral infarction in the absence of anticoagulation therapy. Current guidelines recommend a secondary prevention regimen of antiplatelet agents to prevent stroke recurrence in patients diagnosed with CS and for whom the AF status is unknown. Long-term cardiac rhythm monitoring can reveal occult AF that may otherwise be missed by conventional short-term monitoring [2]. Since September 2016, insertable cardiac monitors (ICMs) for patients with CS have been covered by insurance in Japan.

The term “embolic stroke of undetermined source” (ESUS) has been proposed to describe CS that is not lacunar and is not associated with proximal arterial stenosis or a recognizable cardioembolic source [1]. Two international ESUS trials demonstrated that oral anticoagulants (rivaroxaban and dabigatran) were not superior to aspirin for the prevention of recurrent stroke after ESUS [3,4], although a secondary analysis in the RE-SPECT ESUS (Randomized, Double-Blind Evaluation in Secondary Stroke Prevention Comparing the Efficacy and Safety of the Oral Thrombin Inhibitor Dabigatran Etexilate Versus Acetylsalicylic Acid in Patients With Embolic Stroke of Undetermined Source) study demonstrated that, compared with aspirin, dabigatran was associated with a lower risk of recurrent stroke among Japanese patients with ESUS [5]. In Japan, magnetic resonance imaging (MRI) is widely used in the diagnosis of stroke. The Japanese guidelines indicate that MRI is essential in the selection of candidates with CS eligible for ICM implantation [6]. Branch atheromatous disease (BAD) is a single subcortical infarction larger than lacunar stroke in the territories of deep perforators without relevant arterial stenosis [7]. The Japanese guidelines on the clinical indications for ICMs recommend that BAD should not be considered as an indication because it results from a nonembolic mechanism [6]. These procedural differences between Japan and Western countries may impact the detection rate and predictors of AF in patients with CS. However, available data on Japanese patients are limited to small retrospective studies. Furthermore, additional information about AF detection, including the number of episodes, cumulative episode duration, anticoagulation initiation (type and dose of regimen and time of initiation), rate of catheter ablation, role of atrial cardiomyopathy, and stroke recurrence (time of recurrence and cause of the recurrent event), was not provided in the vast majority of previously published studies [8,9].

This study aims to clarify the proportion and timing of AF detection via ICMs in patients diagnosed with CS in Japan. Additionally, we aim to identify risk stratification criteria using real-world data, which could then be used in clinical practice to predict occult AF, identify optimal candidates for ICM implantation, and inform the development of diagnostic criteria.

## Methods

### Study Design

The LOOK (a multicenter observational study on the detection of AF using insertabLe cardiac mOnitors in patients with cryptOgenic stroKe) registry is an observational, multicenter, prospective registry of patients who have been diagnosed with CS and implanted with an ICM. The Medtronic CareLink Network is being used to remotely transmit the device data.

### Ethics Approval

Ethical approval for this study was obtained from the ethics review committee of Nippon Medical School (B-2019-043) and from the relevant ethics committees of all participating centers. Written informed consent is required from all patients or their family members before study participation. This study is registered with the University hospital Medical Information Network (UMIN) Clinical Trial Registry (UMIN000039809).

### Patient Population

Patient enrollment for this ongoing study started in February 2020 in 24 medical institutions throughout Japan. The inclusion criteria for this study are as follows: (1) patients who have been diagnosed with CS according to the Japanese diagnostic criteria and have been implanted with an ICM (Reveal LINQ), and (2) patients aged 40-90 years. The main exclusion criterion is the presence of contraindications for MRI. A full description of the inclusion and exclusion criteria is presented in Textbox 1.

Inclusion and exclusion criteria.
**Inclusion criteria**
Patients of either sex, between 40 and 90 years of agePatients diagnosed with cryptogenic stroke and implanted with an insertable cardiac monitorPatients (or their legal representatives) who have given written consent
**Exclusion criteria**
Patients with a history of atrial fibrillation and atrial flutterPatients with permanent contraindications or indications for oral anticoagulantsApplicable patients with pacemaker or implantable defibrillator implantationMagnetic resonance imaging–contraindicated patientsPatients diagnosed with life expectancy within 2 years due to some diseaseAn inappropriate decision made by the investigator

### Data Collection

The study data, such as patient background, laboratory data, coagulation test, B-type natriuretic peptide, physiological examination (electrocardiogram [ECG], transthoracic echocardiography, transesophageal echocardiography [TEE], and carotid echocardiography), neuroimaging examination, Mini-Mental State Examination (MMSE), modified Rankin Scale (mRS), and presence of cardiovascular events, gastrointestinal bleeding, and other adverse events, or death (Table 1 and Textbox 2), will be stored on an encrypted website and will be accessible only to study researchers with appropriate training and ethics review board approval. Data monitoring will be performed independently by the study steering committee.

**Table 1 table1:** Overview of study schedule.

Survey items	Baseline survey	6 months (±30 days)	12 months (±30 days)	24 months (±30 days)
Consent withdrawal/visit status/health confirmation		✔	✔	✔
Patient background/history	✔			
Blood count, biochemistry, coagulation test, BNP^a^	✔	✔	✔	✔
Physiological examination (ECG,^b^ TTE,^c^ TEE,^d^ carotid echocardiography)	✔			
Brain MRI^e^ examination	✔	✔	✔	✔
MMSE^f^	✔		✔	✔
mRS^g^	✔	✔	✔	✔
Presence of cardiovascular events, gastrointestinal bleeding, other adverse events, or death		✔	✔	✔

^a^BNP: B-type natriuretic peptide.

^b^ECG: electrocardiogram.

^c^TTE: transthoracic echocardiography.

^d^TEE: transesophageal echocardiography.

^e^MRI: magnetic resonance imaging.

^f^MMSE: Mini-Mental State Examination.

^g^mRS: modified Rankin Scale.

Detailed survey items in this study.
**Patient characteristics**
Age, sex, body mass index, prestroke modified Rankin Scale (mRS) score, antithrombotic therapy before the index case, previous stroke, hypertension, dyslipidemia, diabetes mellitus, alcohol intake, smoking, peripheral artery disease, history of cancer, education level, and CHA_2_DS_2_-VASc (Congestive Heart Failure, Hypertension, Age [≥75 years], Diabetes, Stroke/Transient Ischemic Attack, Vascular Disease, Age [65-74 years], Sex [Female]) score
**Neuroimaging**
Distribution of infarct lesions, infarct size, number of infarcts, major vessel occlusion, intra-arterial signal signs, susceptibility vessel signs, Diffusion-Weighted Imaging—Alberta Stroke Program Early Computed Tomography Scores, natural recanalization, hemorrhagic transformation, number and location of cerebral microbleeds, old cortical lesions, and recurrence of stroke after magnetic resonance imaging
**Electrocardiogram (ECG) and Holter ECG**
Deep terminal negativity of the P-wave V1, P-wave terminal force in lead V1, P axis, PR interval, heart rate–corrected QT interval, and the number and percentage of atrial premature contractions and ventricular premature contractions
**Blood examination**
Routine blood biochemistry examinations, including creatinine clearance and measurements of D-dimers, C-reactive protein, brain natriuretic peptide (BNP), and N-terminal prohormones of the BNP
**Transthoracic echocardiography and transesophageal echocardiography**
Left atrium diameter, left atrial volume index, valvular disease, right to left shunt, aortic plaque thickness and morphology, spontaneous echo contrast, left atrial appendage filling and emptying velocity, left ventricular ejection fraction, atrial septal aneurysm, and strand readings
**Carotid ultrasound**
Max intima-media thickness, plaque morphology, internal carotid artery stenosis as assessed by the European Carotid Surgery Trial method, peak systolic velocity, and end diastolic velocity
**Incidence of recurrent stroke or transient ischemic attack**

**Use and type of oral antithrombotic therapy and antiarrhythmic drugs**

**Stroke severity assessed using the mRS and the National Institutes of Health Stroke Scale**

**Cognitive status evaluated through the Mini-Mental State Examination**

**Cardiovascular events, gastrointestinal bleeding, cancer, other adverse events, or death**

### Sample Size

Recent retrospective observational ICM studies have demonstrated that major vessel occlusion (n=84) and frequent premature atrial contractions (n=66) were associated with AF detection after adjustment for risk factors and comorbidities, respectively [8,9]. A subanalysis of the CRYSTAL AF (Cryptogenic Stroke and Underlying AF) study (including 221 patients with a 30% AF detection rate) demonstrated that older age and longer PR interval were associated with an increased likelihood of detecting AF [10]. On the basis of the results of these previous studies, we decided to enroll 200 patients in this observational study to perform statistical analyses, including multivariate regression analysis, with sufficient statistical power.

### Data Analysis Plan

Table 1 presents an overview of the protocol schedule for this study. Categorical variables will be expressed as frequencies and percentages, whereas continuous variables will be expressed as mean with SD or median with IQR, as appropriate. Patient characteristics, medical history, vital signs, laboratory data, the CHA_2_DS_2_-VASc (Congestive Heart Failure, Hypertension, Age [≥75 years], Diabetes, Stroke/Transient Ischemic Attack, Vascular Disease, Age [65-74 years], Sex [Female]) score, neuroimaging characteristics, ECG characteristics, TEE characteristics, MMSE score, mRS score, and stroke recurrence will be compared between patients with AF and patients without AF (Textbox 2). Intergroup differences will be assessed using the chi-square test or the Wilcoxon rank-sum test, as appropriate. The Yates correction or the Fisher exact test will be used if the validity conditions for the chi-square test are not met (theoretical number <5). Furthermore, we will obtain additional information regarding the number of AF episodes, duration of cumulative AF episodes, and time of anticoagulation initiation. We will investigate the rate of initial AF detection within the initial 6, 12, and 24 months after ICM implantation using Kaplan-Meier survival estimates. Cox proportional hazards regression models will be fitted to various baseline characteristics for the prediction of AF. Receiver operating characteristic curve analysis will be performed to assess the predictive accuracy of a variable in AF detection. All analyses will be performed via JMP version 13 (SAS Institute Inc), with *P*<.05 indicating statistical significance.

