## Discussion

### Principal Findings

Recent meta-analyses demonstrate that, compared with short-term monitoring, prolonged cardiac rhythm monitoring is associated with higher rates of AF detection, a higher incidence of anticoagulation initiation, and reduced stroke recurrence in patients with CS [11]. However, these studies were mainly conducted in Western countries, and the generalizability of these findings to Asian populations is unclear. We are therefore conducting this study, in which we will recruit patients prospectively and identify the proportion of patients with AF to effectively compare the characteristics and outcomes with respect to the presence and absence of AF in patients with CS in Japan.

Some testing biases are affected by geographic location; for example, brain MRI is used less frequently in European patients with ESUS [12]. However, there is better access to MRI in Japan, and it is often implemented upon hospital admission as well as during follow-ups. Furthermore, MRI is necessary for the selection of candidates for ICMs according to Japanese guidelines [6]. This study is thus investigating detailed MRI findings, such as the presence of lesion patterns, susceptibility vessel signs, hemorrhagic transformation, old cortical lesions, and new asymptomatic lesions, during follow-up.

Recent evidence indicates that atrial cardiomyopathy, diagnosed by the presence of serum or electrocardiographic biomarkers, leads to AF and may result in thromboembolism even before AF manifests [13,14]. In this study, we are investigating not only the left atrial diameter but also the left atrial volume index and P-wave parameters in ECG, including P-wave terminal force in V1. Atrial cardiomyopathy may explain a proportion of ESUS cases, although AF is currently the sole diagnostic criterion for atrial thrombogenic potential. ARCADIA (AtRial Cardiopathy and Antithrombotic Drugs In Prevention After Cryptogenic Stroke) is an ongoing trial investigating whether anticoagulant therapy reduces the occurrence of stroke in patients with atrial cardiomyopathy without known AF [15]. This study will clarify the association among atrial cardiomyopathy markers, AF, and stroke recurrence in patients with CS.

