A previous retrospective study reported that plasma brain natriuretic peptide (BNP) levels were elevated in the acute phase of stroke but were substantially reduced in patients with cardioembolic stroke [16]. This suggests that fluctuating levels of BNP or N-terminal prohormone of BNP (NT-proBNP) may be associated with occult paroxysmal AF. However, serial changes in plasma BNP or NT-proBNP levels in patients with CS and ICMs have not been fully investigated. In this study, we will be conducting serial measurements of BNP or NT-proBNP levels.

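### Comparing stroke recurrence between patients ever and never found to have AF pools time before and after detection, so the result cannot be read as an effect of AF or of its treatment

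*Protocol article*

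**What the plan says.** Textbox 1 of the protocol article excludes patients with previous AF or flutter. A patient with AF in this registry is therefore one in whom the monitor finds it after implantation, at any time up to 24 months.

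The Data Analysis Plan then says that "MMSE score, mRS score, and stroke recurrence will be compared between patients with AF and patients without AF", and the next sentence assigns the method: "Intergroup differences will be assessed using the chi-square test or the Wilcoxon rank-sum test, as appropriate". Yates or Fisher is the fallback for small expected counts. The Methods paragraph of the Abstract repeats the comparison for recurrence and functional outcomes.

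Time-to-event methods are named for AF detection only: "We will investigate the rate of initial AF detection within the initial 6, 12, and 24 months after ICM implantation using Kaplan-Meier survival estimates" and "Cox proportional hazards regression models will be fitted to various baseline characteristics for the prediction of AF". The start of anticoagulation is collected ("we will obtain additional information regarding the number of AF episodes, duration of cumulative AF episodes, and time of anticoagulation initiation") but is not linked to the recurrence comparison.

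The Discussion states the intended use: "This study will clarify the association among atrial cardiomyopathy markers, AF, and stroke recurrence in patients with CS".

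**The concern.** The group label depends on something that happens during the same follow-up in which recurrences are counted. A stroke in month 3 of a patient whose AF is found in month 10 counts against the AF group, although that patient was then undetected. A stroke in month 15 of the same patient also counts against the AF group, although treatment may have changed in between. The article itself expects such a change: it associates prolonged monitoring with "a higher incidence of anticoagulation initiation, and reduced stroke recurrence in patients with CS".

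The risk in the AF group is thus a mixture of two periods that may have different hazards, weighted by when detection happened to occur. If the contrast is published as the association of AF with recurrence, readers may take it as the risk carried by AF, or as the benefit of finding and treating it. It is neither, and it can miss either in size or in direction.

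**Working it through.** **No planned figure to reproduce.** The Sample Size section gives 200 patients without a power, an effect size or a recurrence rate. The check is on what the stated comparison would return when the truth is known.

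**Inputs from the article.** 30% AF detection (the cited subanalysis in Sample Size), 24 months of follow-up, 213 enrolled. This gives 0.30 × 213 = 64 patients with AF and 149 without.

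**Assumptions, not in the article.** Base recurrence hazard h = 0.05 per year; cumulative detection of 6%, 10%, 14%, 21% and 30% at 1, 3, 6, 12 and 24 months; complete follow-up; monitoring continues after a recurrence.

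**Step 1: time before detection.** Of the patients with AF, 20%, 13.3%, 13.3%, 23.3% and 30% are detected in successive intervals with midpoints 0.5, 2, 4.5, 9 and 18 months. The mean detection time is 0.1 + 0.27 + 0.6 + 2.1 + 5.4 = 8.47 months, so 8.47/24 = 35% of the AF group's time is pre-detection. With mean detection at 6 or 12 months the share is 25% or 50%.

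**Step 2: the ever/never risk ratio.** Let a and b be the hazard multiples before and after detection. A patient detected at T years has recurrence risk 1 − exp(−h[aT + b(2 − T)]), averaged over T. A never-detected patient has 1 − exp(−0.10) = 0.0952. A hand approximation is RR ≈ (8.47a + 15.53b)/24.

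| Truth | Hand approximation | AF risk | No-AF risk | RR |
|---|---|---|---|---|
| a = 3, b = 1 | (25.4 + 15.5)/24 = 1.71 | 0.1553 | 0.0952 | 1.63 |
| a = 1, b = 0.4 | (8.47 + 6.21)/24 = 0.61 | 0.0592 | 0.0952 | 0.62 |
| a = 2, b = 0.8 | (16.9 + 12.4)/24 = 1.22 | 0.1146 | 0.0952 | 1.20 |
| a = 2, b = 2 | 2.00 | 0.1813 | 0.0952 | 1.90 |
| a = 1, b = 1 | 1.00 | 0.0952 | 0.0952 | 1.00 |

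In the first row, 25.4/(25.4 + 15.5) = 62% of the AF group's recurrences precede detection. With base rates of 3% and 8% per year the first row gives 1.66 and 1.59, and the second 0.62 and 0.63. The detection pattern matters more: for early (mean 6 months) and uniform (mean 12 months) detection, the second row becomes about 0.56 and 0.71, and the third about 1.09 and 1.36.

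**Step 3: unequal follow-up alone.** Set a = b = 1 and lose 10% or 20% of patients over 24 months, unrelated to recurrence. The risk ratio is 1.03 or 1.07, with mean follow-up of 23.4 against 22.5 months, or 22.7 against 21.1. With constant detection hazard and 5%, 10% or 15% loss per year it is 1.05, 1.09 or 1.14. For scale, take about 6.1 and 14.2 recurrences in 64 and 149 patients: the standard error of log RR is √(1/6.1 − 1/64 + 1/14.2 − 1/149) = 0.46, against ln 1.07 = 0.07.

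**Step 4: what separated reporting returns.** For a = 3, b = 1 in 213 patients, with time counted to first recurrence:

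| State | Events | Person-years | Rate per year |
|---|---|---|---|
| Never detected | 14.2 | 283.8 | 0.05 |
| Before detection | 6.2 | 41.2 | 0.15 |
| After detection | 3.7 | 74.7 | 0.05 |

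The table shows the pattern that the single risk ratio hides. A time-dependent contrast of detected with not-yet-detected time gives (3.7/74.7)/((6.2 + 14.2)/(41.2 + 283.8)) = 0.050/0.063 = 0.80. That is a correct answer to its own question, but it is not the effect of having AF, because undetected AF sits in the reference.

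**The case against.** The stated aims are the proportion and timing of AF detection and the prediction of AF. These rest on Kaplan-Meier and on Cox models with baseline covariates, which the defect does not touch. Recurrence is one item in a long comparison list, and the Discussion speaks of association, not causation. An ever/never description is legitimate in a registry. With complete follow-up and no treatment effect the test is valid under the null (risk ratio 1.00), and a constant hazard ratio of 2 appears as 1.90. All of this stands, and it limits how much weight the point carries.

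It does not remove the point. The article fixes the groups, the outcome and the test, and assigns its survival methods elsewhere, so this is a stated choice and not a detail left to a fuller plan. It also announces a conclusion on AF and recurrence.

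Three stronger readings are tempting and are not supported:

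- **That the contrast is worthless.** It remains a valid description of who had a recurrence.
- **That it suffers from immortal time.** Recurrences before detection are counted in the AF group, so that time is not event-free by construction. What remains is unequal follow-up, which is small in Step 3.
- **That the serial BNP data share the defect.** The article says only "In this study, we will be conducting serial measurements of BNP or NT-proBNP levels". It states no comparison of those serial values by AF status.

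MMSE and mRS are also measured at baseline (Table 1), and the Data Analysis Plan does not say which time point is compared. The point is therefore confined to stroke recurrence.

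**Conclusion.** The concern holds for stroke recurrence. The planned ever/never comparison mixes pre-detection and post-detection time and cannot be read as the effect of AF, or of its treatment, on recurrence. Under the assumed rates it attenuates a pre-detection hazard ratio of 3 to a risk ratio of about 1.6, and it turns no AF effect with a post-detection hazard ratio of 0.4 into about 0.6, so that AF looks protective.

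Only the 30%, the 24 months and the 213 come from the article. The recurrence rate, the detection curve and the hazard ratios are assumptions, and the distortion depends on the hazard changing at detection. Attrition unrelated to recurrence adds only a small bias. Comparisons of baseline characteristics by later AF status, and the analyses of AF detection itself, are not affected.

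**What to change.** In the Data Analysis Plan:

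1. Classify each recurrence as before or after first detection of AF by the monitor.
2. Report events and person-years separately for never-detected, pre-detection and post-detection time, with post-detection time split by anticoagulation where numbers allow. Present this as description, since pre-detection time is identified by a later event.
3. Base any test on time to recurrence, with AF detection as a single time-dependent covariate or with a landmark (for example 6 months). State that it compares detected with not-yet-detected AF.
4. Label the ever/never chi-square comparison of recurrence descriptive only, and word the Discussion's statement on AF and recurrence to match.
5. Record the date of each recurrence if this is not already done. Textbox 2 lists incidence; time of recurrence appears in the Introduction only as a gap in earlier studies.

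The cost is analysis wording and possibly one date field. The drawback is precision: about 4 of 213 patients would have a post-detection recurrence under the assumed rates. A second time-dependent term for anticoagulation, which would closely track detection wherever treatment starts promptly, is not realistically estimable and should not be planned.

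### MMSE and mRS outcomes are to be compared by AF status with unadjusted tests only, so a follow-up difference may partly reflect age; an age-adjusted analysis should be added

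*Protocol article*

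**What the plan says.** The Data Analysis Plan of the protocol article puts MMSE, mRS and stroke recurrence in the list of items to be compared by AF status. The sentence that follows gives the method: "Intergroup differences will be assessed using the chi-square test or the Wilcoxon rank-sum test, as appropriate". Yates or Fisher replaces chi-square when expected counts are small, and P<.05 applies to all analyses.

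Outcomes are included, not only baseline traits. The Abstract (Methods) says that "cognitive status, stroke recurrence, and functional outcomes will be compared between patients with AF and patients without AF". Principal Findings gives as a purpose of the study to "effectively compare the characteristics and outcomes with respect to the presence and absence of AF in patients with CS in Japan". Table 1 schedules MMSE at baseline, 12 and 24 months, and mRS at baseline, 6, 12 and 24 months.

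The other methods named are Kaplan-Meier, Cox and ROC, and all have AF detection as the outcome. For the regression: "Cox proportional hazards regression models will be fitted to various baseline characteristics for the prediction of AF". The Sample Size section mentions multivariate regression but does not tie it to MMSE or mRS.

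The same section reports, from a cited ICM subanalysis, that "older age and longer PR interval were associated with an increased likelihood of detecting AF". Textbox 2 collects "Age, sex, body mass index, prestroke modified Rankin Scale (mRS) score" and education level.

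**The concern.** One rule covers both the baseline table and the outcome comparison, and it suits only the first. If patients with detected AF are older, and older patients score worse on MMSE and mRS, the two groups will differ at follow-up even if AF itself contributes nothing. A P value below .05 at 24 months could then be read as a link between AF and cognition or function when it partly shows age. The variables needed to separate the two are already collected, and the stated tests use none of them. The tests also ignore the baseline score, which usually carries much of the information about the follow-up score.

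**Working it through.** The plan has no figure of its own for this contrast. The 200 patients are set by analogy with earlier studies, without an effect size, SD or power, so there is nothing to reproduce.

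**Inputs from the documents.** N = 200 and a 30% AF detection rate in the cited subanalysis (Sample Size), which gives 0.30 × 200 = 60 AF and 140 non-AF patients. Alpha is 0.05 (Data Analysis Plan); two-sided is assumed.

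**Inputs assumed, because the documents give none.** Scores and age are in SD units.
- Age gap g between AF and non-AF patients: 0.3, 0.5 or 0.7.
- Correlation b of age with baseline score: −0.2 or −0.4.
- Coefficient ρ of baseline on follow-up score (close to their correlation): 0.5, 0.7 or 0.8.
- Direct effect c of age on follow-up score: −0.1.
- True AF effect: zero.

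**Step 1, standard error of the raw difference.** √(1/60 + 1/140) = 0.154 SD.

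**Step 2, difference produced by age alone.** Bias = g × (ρb + c). The smallest age slope is 0.5 × (−0.2) − 0.1 = −0.20. The largest is 0.8 × (−0.4) − 0.1 = −0.42.

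**Step 3, rejection with no AF effect** (simulation, 1,500 runs per setting):

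| Age gap (SD) | Bias from the formula (SD) | Unadjusted Wilcoxon rejects |
|---|---|---|
| 0 | 0 | 4%–6% |
| 0.3 | −0.06 to −0.13 | 7%–12% |
| 0.5 | −0.10 to −0.21 | 8%–26% |
| 0.7 | −0.14 to −0.29 | 14%–44% |

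Linear regression on AF status, age and baseline score rejects in about 4% to 6% of runs in every setting, with bias near zero. Adjusting for age alone also removes the bias here, because age is the only route from group to score in this set-up.

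**Step 4, the same on the MMSE scale.** Assume AF patients are 5 years older, MMSE falls 0.10 to 0.15 points per year, and the SD is 3. The bias is 5 × 0.10 = 0.5 to 5 × 0.15 = 0.75 points. The standard error is 3 × 0.154 = 0.463, so z = 1.08 to 1.62 and rejection is about 19% to 37%. If the age SD is 10, these slopes imply an age–MMSE correlation of 0.10 × 10/3 = 0.33 to 0.15 × 10/3 = 0.50. That is stronger than the 0.20 to 0.42 in Step 2, so this is one scenario and not a bound.

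**Step 5, precision from the baseline score.** The standard error is multiplied by √(1 − ρ²): 0.87 at ρ = 0.5 (13% lower) and 0.71 at ρ = 0.7 (29% lower). The difference detectable with 80% power is (1.960 + 0.842) × 0.154 = 0.43 SD unadjusted, and 0.37 or 0.31 SD with the baseline score.

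The calculation treats the score as continuous. No separate figure was worked out for mRS; for mRS only the direction of the argument carries over.

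**The case against.** The strongest reply is that this is a secondary, descriptive comparison. The stated objectives are the proportion and timing of AF detection and the prediction of AF, and those have suitable time-to-event methods. Nowhere does the article claim to estimate an effect of AF on cognition or function. A rank test of whether two groups differ is valid for that plain question. This stands: a reader might infer that the study's main results are biased, or that the test itself is invalid, and the documents support neither.

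The follow-up time point is an inference. The Data Analysis Plan names no visit, and the scores sit in a list made up mostly of baseline traits. The Abstract, Principal Findings and Table 1 make the follow-up reading the natural one. Because chi-square is also allowed, a dichotomised mRS might not be rank-tested, but it would still be unadjusted.

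A full analysis plan may contain adjusted models, and the article does not say that the listed tests are the only ones. That is fair, but the article does assign a specific method to this comparison, so the point does not rest on silence.

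A reader might also take age as known to differ by AF status in this cohort, or take 19% to 37% as the false-positive rate. The age link comes from one cited subanalysis, with no size given, and the percentages rest wholly on assumed inputs.

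Finally, adjusting for baseline MMSE or mRS is not neutral. Both are measured after the index stroke, and the Introduction suspects occult AF as a major cause of such strokes. These scores may therefore partly be consequences of AF, and adjusting for them changes the question. Age, education and prestroke mRS are not open to this objection.

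**Conclusion.** The point holds as a limited one. The article states only unadjusted tests for comparing cognition and function by AF status, while citing age as a correlate of AF detection and collecting the variables needed to adjust for it. A follow-up difference may therefore partly reflect age.

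The size is not known from the documents. Under the assumed age gaps and correlations, with no AF effect, the unadjusted test rejects between about 7% (near nominal) and about 44% of the time; with no age gap it is valid. The direction of the bias does not depend on these values, provided AF patients are older and age goes with worse scores. The precision gain of 13% to 29% in standard error assumes a baseline to follow-up correlation of 0.5 to 0.7. The documents do not support a claim that the detection or prediction aims are affected.

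**What to change.** Keep the chi-square, Fisher and Wilcoxon tests for baseline description. For the outcomes, add:

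- **MMSE at 12 and 24 months:** regression on AF status, adjusted for age and education.
- **Follow-up mRS:** an ordinal model on AF status, adjusted for age and prestroke mRS.
- **A second model for each outcome** that also includes baseline MMSE or baseline mRS, reported as the difference in change since the index stroke and not as the total difference by AF status.

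Use NIHSS as a covariate only if a baseline value is available: Textbox 2 lists it, but Table 1 does not schedule it.

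The cost is a change of analysis wording, slightly more analysis work, and reliance on model assumptions (such as proportional odds, if that ordinal model is used) for a secondary analysis. No visit, measurement or patient is added.
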